### Sample size

The sample size estimation of 1,050 was based on an anticipated overall failure rate of 5 %, as suggested by short-term follow-up in the single centre pilot study, and a non-inferiority margin of 5 % (a relative increase of 100 %), with a one-sided alpha = 0.05, 90 % power and 10 % loss to follow-up.

Pooled data from a planned interim analysis demonstrated that the true event rate is likely to be closer to 12.5 %. To account for this, we adjusted the non-inferiority margin to 7.5 % (a relative increase of 60 %). As the final control group failure rate remains unknown, recruitment will continue as planned until October 2015 to achieve the largest possible sample size within the original target, and to optimise the potential utility of subgroup analyses. The DMC and ethics committee approved this amendment.

Sample size calculations for binary outcomes were performed in Stata (StataCorp LP, College Station, TX, USA).

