**Methods:**

The OVIVA trial is a parallel group, randomised (1:1), un-blinded, non-inferiority trial conducted in thirty hospitals across the UK. Eligible participants are adults (>18 years) with a clinical syndrome consistent with a bone, joint or metalware-associated infection who have received ≤7 days of intravenous antibiotic therapy from the date of definitive surgery (or the start of planned curative therapy in patients treated without surgical intervention). Participants are randomised to receive either oral or intravenous antibiotics, selected by a specialist infection physician, for the first 6 weeks of therapy. The primary outcome measure is definite treatment failure within one year of randomisation, as assessed by a blinded endpoint committee, according to pre-defined microbiological, histological and clinical criteria. Enrolling 1,050 subjects will provide 90 % power to demonstrate non-inferiority, defined as less than 7.5 % absolute increase in treatment failure rate in patients randomised to oral therapy as compared to intravenous therapy (one-sided alpha of 0.05).

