Initial recruitment of study patients was slower than anticipated. This was primarily due to delays in site setup and in establishing mechanisms for the timely identification and referral of potential participants to the research teams. Recruitment was also adversely affected by a surprising number of patients who, having read the PIS and understanding the principle of equipoise, requested oral therapy rather than IV therapy. In order to achieve the recruitment target, we implemented a web-based network site, monthly teleconferences and recruitment drives, and requested an extension without additional cost to the funding agency.

At the second planned interim analysis, the overall primary endpoint event rate (12.5 %) was significantly higher than had been predicted from the single centre pilot study (5 %); reasons for this might include stochastic variation related to a small sample, the effect of recruitment at a single specialist centre or a combination of factors. In order to accommodate this unexpected finding, and with appropriate ethical permission and endorsement from the DMC, we elected to amend the non-inferiority margin from 5 % to 7.5 %. This figure remains within published guidelines, which suggest that a non-inferiority margin of 10 % is appropriate for most therapeutic intervention trials in infection [33]. We therefore believe that the non-inferiority margin remains appropriate for this trial and is unlikely to jeopardise the utility of the results.

Despite its limitations, the trial will be the largest study of its type addressing this question of oral versus IV antibiotic therapy in bone and joint infection, and is likely to have important implications for patients and healthcare practitioners in the field of orthopaedic infection, and for the health economy.

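### The 1,050 matches a 5% v 10% difference-detection formula rather than a non-inferiority calculation, and the 90% power quoted for the 7.5-point margin is understated (about 97% at equal 12.5% rates, 945 evaluable)

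*Protocol article*

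**What the plan says.** The Sample size section of the protocol article states: "The sample size estimation of 1,050 was based on an anticipated overall failure rate of" 5%, a figure taken from early follow-up in the single-centre pilot. The other inputs are "a non-inferiority margin of 5 % (a relative increase of 100"%), "with a one-sided alpha = 0.05, 90 % power and 10 % loss to follow-up". The section names Stata as the software but not the formula, and it states no separate failure rate for the oral arm.

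The same section then reports: "Pooled data from a planned interim analysis demonstrated that the true event rate is likely to be closer to" 12.5%. It moves the margin to 7.5 points, described as a 60% relative increase. It adds that the final control-group rate is unknown and that recruitment will go on towards the largest sample possible within the original target. In the Discussion the authors write "we elected to amend the non-inferiority margin from" 5% to 7.5%, with ethics and DMC endorsement, and note that published guidance allows 10%.

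The Methods part of the abstract describes the amended design: "Enrolling 1,050 subjects will provide" 90% power at the 7.5-point margin, one-sided alpha 0.05. Under Primary endpoint, non-inferiority is met if the upper limit of the 90% interval for oral minus intravenous lies below 7.5 points.

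**The concern.** Power in a non-inferiority trial is the chance that the confidence limit clears the margin when oral treatment is in truth acceptable, usually when the two arms have equal rates. A formula that sets the arms at 5% and 10% answers another question, namely the chance of detecting a difference as large as the margin. If the truth were 5% v 10%, the difference would equal the original margin and the trial's rule would succeed only about 5% of the time. So that formula does not give the power of the test this trial performs.

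The 90% was attached to the 5% rate and 5-point margin in the Sample size section, and it reappears unchanged in the abstract beside a different margin, adopted because of a different event rate. The margin sets how many extra failures may still be called non-inferior, and it was widened after pooled interim data. The article gives no power at the old margin and, at the new one, a figure its inputs do not return. A reader therefore cannot see what the change bought.

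**Working it through.** **Inputs** (Sample size section and abstract): 1:1 allocation; one-sided alpha 0.05 (z = 1.645); 90% power (z = 1.282); 10% loss, so 1,050 × 0.9 = 945 evaluable, 472.5 per arm; 5% rate with 5-point margin originally; 12.5% rate with 7.5-point margin as amended. (1.645 + 1.282)² ≈ 8.564.

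**1. Reproducing 1,050.** Two-proportion formula, 5% v 10%, unpooled variance:

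n per arm = 8.564 × (0.05 × 0.95 + 0.10 × 0.90) / 0.05² = 471.01, so 472. Total 944; 944 / 0.9 = 1,048.9, so 1,049 (1,050 if each arm is rounded up).

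With pooled variance under the null: 474 per arm, 948, and 948 / 0.9 = 1,053.3, so 1,054. Both agree with the stated figure. A continuity correction (1,140 after loss) and two-sided alpha 0.05 (1,294) do not.

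**2. Non-inferiority formula on the same inputs**, both arms at 5%:

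n per arm = 8.564 × 2 × 0.05 × 0.95 / 0.05² = 325.4, so 326. Total 652; 652 / 0.9 = 724.4, so 725. The Farrington-Manning version gives 357 per arm, 714, and 794 after loss. Neither is near 1,050.

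**3. Power at the amended margin**, both arms at 12.5%:

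SE = √(2 × 0.125 × 0.875 / 472.5) = 0.02152

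Power = Φ(0.075 / 0.02152 − 1.645) = Φ(1.841) = 96.7%

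Farrington-Manning gives 96.4%. With all 1,050 evaluable the simple formula gives 97.9%. The apparent original method, applied to 12.5% v 20% with 945 evaluable, gives 93.2% (91.8% with continuity correction). None of these is 90%.

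**4. Patients needed for 90% power at 7.5 points**, both arms at 12.5%: 8.564 × 2 × 0.125 × 0.875 / 0.075² = 333.04, so 334 per arm, 668 evaluable, and 668 / 0.9 = 742.2, so 743 enrolled.

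**5. Figures relevant to the amendment**, both arms at 12.5%:

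| Quantity | 945 evaluable | 1,050 evaluable |
|---|---|---|
| Power at 5 points | 75.1% | 78.9% |
| Margin giving 90% power | 6.3 points | 6.0 points |
| Power at 7.5 points | 96.7% | 97.9% |

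The 6.3 is (1.645 + 1.282) × 0.02152 = 0.0630. Keeping 5 points with 90% power would have needed 750 per arm, 1,500 evaluable, about 1,667 enrolled.

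**6. Sensitivity of the 97%** (assumed scenarios, 945 evaluable):

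- Oral truly 1 point worse, 12.5% v 13.5%: SE = √((0.125 × 0.875 + 0.135 × 0.865) / 472.5) = 0.02188; power = Φ(0.065 / 0.02188 − 1.645) = Φ(1.326) = 90.8%.
- Common rate 19%: SE = √(2 × 0.19 × 0.81 / 472.5) = 0.02552; power = Φ(0.075 / 0.02552 − 1.645) = 90.2%.

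**7. The relative increase.** 7.5 / 12.5 = 60%, which is right if 12.5% is the intravenous rate. The article calls it pooled. If the arms were 7.5 points apart around a pooled 12.5%, they would be 8.75% and 16.25%, and 7.5 / 8.75 = 86%.

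**The case against.** Several objections have force.

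- **The 1,050 can be reproduced.** A standard one-sided formula returns it almost exactly, so it would be too strong to say that it cannot be obtained from the stated inputs. This stands as an account of where the figure came from. It does not make it a non-inferiority calculation, because the Primary endpoint rule tests something else. An article may leave the formula to the full protocol, but the power it does state should fit the design it describes.
- **The error is on the safe side.** More patients are enrolled than the equal-rates formula requires, and power is understated. The type I error and the decision rule do not depend on the power figure. This stands in full.
- **97% is a favourable case.** It assumes equal rates of exactly 12.5% and full recruitment, whereas the article says the control rate is unknown and treats 1,050 as a ceiling. This stands, so the figure must carry its assumptions.
- **60% is correct arithmetic.** It uses the same convention as 5/5 = 100%, and under equal rates the pooled rate is the control rate. This stands; only the base needs stating.

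A reader might infer from the 6.3 points that the margin was widened further than the trial needed. The documents do not support that. It would hold only with equal 12.5% rates, full recruitment and a bare 90% target; the article never says the margin was chosen as the smallest giving 90%, and the Discussion offers a separate guideline-based reason. Nor does the article say that 90% power required 7.5 points. The abstract says only that 1,050 patients provide it.

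**Conclusion.** The point holds as an error in the stated planning figures. The 1,050 corresponds to detecting 5% v 10% (1,049 to 1,054), whereas a non-inferiority calculation with 5% in both arms gives about 725 (794 by Farrington-Manning). The 90% power quoted for the 7.5-point margin is matched by neither method at a 12.5% rate with 945 evaluable: about 97% for the non-inferiority formula with equal rates and about 93% for the apparent original method.

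The consequence is limited. The trial is not under-sized, and the validity of its primary test is unaffected. What suffers is the reader's ability to weigh the margin amendment. That rests on figures the article omits: about 75% power had the 5-point margin been kept, and 90% at about 6.3 points, both assuming 12.5% in each arm and 945 evaluable. These figures inform a judgement on the amendment and do not by themselves show that 7.5 points was excessive.

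**What to change.** In the Sample size section and the Methods part of the abstract:

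1. Name the formula and the failure rate assumed in each arm, and say that 1,050 came from a 5% v 10% calculation if the authors confirm it.
2. Replace the 90% with about 97% power for 12.5% in both arms, a 7.5-point margin and 945 evaluable. Add that this falls to about 91% if oral is truly 1 point worse (12.5% v 13.5%) and to 90% at a common rate of about 19%.
3. State that the 5-point margin would have had about 75% power (79% with all 1,050 evaluable) and that about 6.3 points gives 90%, under equal 12.5% rates.
4. Say that the 60% relative increase takes the pooled 12.5% as the intravenous rate.

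Optionally, because the margin changed after interim data, report the same upper confidence limit against 5 points as a second step once 7.5 points has been cleared. The steps are nested, so this costs no alpha.

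The cost is a paragraph of text and, if the option is taken, one line in the primary results. No further patients or data are needed.

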### Analysis of efficacy

#### Primary endpoint

Based on intention to treat, the proportions of participants experiencing the primary endpoint at one year follow-up (definitive treatment failure as adjudicated by a blinded ERC) will be tabulated by treatment administration group (that is, PO versus IV therapy). If the absolute, upper 90 % confidence interval around the unadjusted difference (oral versus intravenous) is less than 7.5 %, then the criteria of non-inferiority will be met.

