### Trial participants

Participants are recruited from 30 secondary care centres, all of which are NHS hospitals in England or Scotland. All sites currently use 6 weeks of IV antibiotic therapy as their standard initial treatment for some or all categories of bone and joint infection, and all are able to deliver IV antibiotics to patients after discharge from hospital.

Participants are considered for inclusion when an infection specialist reviews a patient with a bone or joint infection. The contact is triggered by routine care pathway, for example, following referral by a surgical team, a referral from primary care direct to infectious disease services, or by following up a laboratory result. Informed consent is obtained from each participant by good clinical practice (GCP) trained research staff after assessing their understanding of the Patient Information Sheet (PIS) [see Additional files 1 and 2]. Eligibility is determined by the inclusion and exclusion criteria listed below.

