### Randomisation

An electronic randomisation service, with telephone backup if necessary, is provided through a clinical trials unit. After confirming the patient’s eligibility, the randomisation service assigns a sequentially allocated study number and informs the investigator of the treatment allocation in real time and by confirmatory e-mail. Randomisation is stratified by site, to take account of variation in clinical practice among centres.

The local clinician or study nurse is responsible for documenting the participant’s enrolment in their clinical notes and for informing the participant’s general practitioner.

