#### Secondary endpoints

Secondary analyses will include: (i) a per-protocol analysis based on all participants who have received at least 4 weeks of randomised therapy and (ii) intention-to-treat and per-protocol analyses in the subgroup with “definite” or “definite”/“probable” infection at randomisation. These secondary analyses will focus on consistency of point estimates and 95 % CI, rather than formal comparison with the 7.5 % non-inferiority margin. We will similarly compare the proportions of participants with secondary endpoints, or the distributions of continuous secondary outcomes (rank sum tests). Subgroup analyses will use interaction tests to determine the consistency of treatment effects by type of infection and infecting pathogen. We record treatment intentions for both intravenous and oral routes at baseline before randomisation. Subgroup analysis will compare efficacy of intravenous versus oral antibiotic therapy according to whether or not rifampicin was used as an adjunctive therapy in the intravenous and oral arms (four subgroups). We will also conduct subgroup analyses according to the clinician’s specific antibiotic intentions, as recorded prior to randomisation.

A survival analysis will be performed to assess post-randomisation surveillance bias, which would present as a delay in time to meeting an endpoint in one randomised group. Other secondary analyses will include regression models (logistic (binary) or quantile (continuous)) to calculate estimates of treatment differences for the primary and secondary endpoints adjusted for age, comorbidity, infecting pathogen and type of surgical intervention.

The statistical analysis plan will be locked prior to analyses being undertaken and will be made freely available at the time of publication.

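### Randomisation is stratified by site, but no stated analysis of the primary endpoint uses site; the cost is a small, conservative loss of precision

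*Protocol article*

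**What the plan says.** The Methods part of the abstract describes a "parallel group, randomised (1:1), un-blinded, non-inferiority trial". Under Trial participants, "Participants are recruited from 30 secondary care centres", and the Background adds that data from 228 participants in a single-centre pilot were moved into the multicentre database. Under Randomisation: "Randomisation is stratified by site, to take account of variation in clinical practice among centres". No other stratification factor is named.

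Under Analysis of efficacy, Primary endpoint, non-inferiority is met if the upper limit of the 90% "confidence interval around the unadjusted difference (oral versus intravenous) is less than" 7.5 percentage points.

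Under Secondary endpoints, the other secondary analyses include "regression models (logistic (binary) or quantile (continuous)) to calculate estimates of treatment differences for the primary and secondary endpoints", which are "adjusted for age, comorbidity, infecting pathogen and type of surgical intervention". Site is not in that list, and the article does not say on which scale the adjusted result will be summarised. The same section says that the per-protocol and infection-certainty analyses "will focus on consistency of point estimates and 95 % CI, rather than formal comparison with the 7.5 % non-inferiority margin". It also announces a separate SAP, locked before analysis, which is not shown here.

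**The concern.** The design restricts randomisation on a factor that the article itself says matters, and then names no analysis of the primary endpoint that uses it. This is not silence left for the SAP to fill: the word unadjusted in the decision rule and the covariate list are both stated choices, and an SAP that followed them would contain no site-adjusted estimate.

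When allocation is balanced within sites, differences between sites contribute almost nothing to the true sampling variance of the treatment difference, but the unadjusted variance formula still counts them. The interval is then somewhat too wide. What is at stake is precision at the 7.5-point margin, not protection against a false claim.

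A separate, smaller matter is the scale of the adjusted analysis. The primary result is a risk difference. A logistic model left in its native form gives an odds ratio, which cannot be set beside that difference without a conversion.

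**Working it through.** **Inputs from the protocol article.** Original failure rate 5% and margin 5 points; one-sided alpha 0.05, power 90%, loss 10%, total 1,050; revised rate 12.5% and margin 7.5 points (all under Sample size). Evaluable: 1,050 × 0.9 = 945, or 472.5 per arm.

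**Assumed inputs.** Between-site ICC of 0 to 0.10. For the simulation, 30 sites, one of 220 and 29 of 25 (220 + 725 = 945).

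**1. The plan's own figure.** Two-proportion formula, 5% against 10%, one-sided, no continuity correction: n per arm = [1.645·√(2 × 0.075 × 0.925) + 1.282·√(0.05 × 0.95 + 0.10 × 0.90)]² / 0.05² = 474. Total 948; 948/0.9 = 1,054 (or 948 × 1.1 = 1,043). The stated 1,050 is reproduced without any allowance for stratification.

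**2. Unadjusted half-width.** At 12.5% in both arms: 1.645 × √(2 × 0.125 × 0.875 / 472.5) = 3.54 points.

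**3. Effect of stratifying by site.** Var(stratified) ≈ Var(unadjusted) × (1 − ICC), so the half-width is multiplied by √(1 − ICC). The one-sided type I error of the unadjusted rule is Φ(−1.645/√(1 − ICC)). The matching between-site SD is √(ICC × 0.125 × 0.875).

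| ICC | Between-site SD (points) | Stratified 90% half-width (points) | Type I error of unadjusted rule |
|---|---|---|---|
| 0 | 0 | 3.54 | 0.050 |
| 0.01 | 3.3 | 3.52 | 0.049 |
| 0.02 | 4.7 | 3.50 | 0.048 |
| 0.05 | 7.4 | 3.45 | 0.046 |
| 0.10 | 10.5 | 3.36 | 0.041 |

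The largest reduction is 3.54 − 3.36 = 0.18 points.

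**4. Simulation (20,000 runs per setting).** The unadjusted Wald limit was compared with a site-stratified Mantel-Haenszel risk difference (Sato variance).
- Type I error at a true difference of 7.5 points: 0.046 to 0.050 unadjusted, 0.049 to 0.053 stratified.
- Power with equal arms: 96.7 to 97.1% unadjusted, 96.7 to 97.5% stratified.
- Neither estimate was biased.

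**5. Where the ICC might lie.** As an illustration only, suppose the 228 pilot participants failed at 5% and all 1,050 at 12.5%. The remaining 822 would fail at (131.25 − 11.4)/822 = 14.6%. The SD between the two cohorts is √(0.217 × 0.783) × 9.6 = about 4 points, and 0.04²/0.1094 is an ICC of about 0.015, before any spread among the other sites. The 5% came from short-term follow-up, so part of that gap may be timing.

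**6. Scale of the adjusted model.** The odds ratio equivalent to +7.5 points at control rate p is [(p + 0.075)/(1 − p − 0.075)] / [p/(1 − p)]:
- p = 5%: 2.71
- p = 10%: 1.91
- p = 12.5%: 1.75
- p = 20%: 1.52

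Conversely, a fixed odds ratio of 1.75 means 6.3 points at 10% control failure and 10.4 points at 20%.

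**The case against.** The strongest reply is that nothing here can harm the conclusion. The unadjusted rule is simple, pre-specified, unbiased and slightly conservative, and in a non-inferiority trial a slightly wide interval makes a false claim no more likely. The gain in simulated power is at most about 0.4 percentage points. At the largest assumed ICC the Mantel-Haenszel rule came out marginally above nominal, at 0.053. Changing the primary analysis after the margin was already amended on interim data also invites questions. All of this stands. It limits the size of the point, but it does not supply a reason to leave the stratification factor out of every stated analysis.

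Two stronger readings are tempting, and the article supports neither.

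- A reader might infer that the primary interval is wider than the design permits. The design sets no interval width, and the 1,050 reproduces from an unstratified formula, so the planned analysis and the planned size agree.
- A reader might infer that the adjusted model cannot be read against the 7.5-point margin. The article speaks of treatment differences and never names the odds ratio, and a logistic fit can be standardised to a risk difference. The model has no stated decision role: it sits among the other secondary analyses, and the primary decision is already on the absolute scale. Leaving out site has no bearing on the scale either; the link function determines that.

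It is also fair that the method of converting a logistic result commonly belongs in the SAP. That part is therefore a request to fix the summary scale, not a claim of error.

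**Conclusion.** The point holds as a modest one. Site is the only named stratification factor, and neither the primary interval nor the listed covariates of the adjusted model use it. The consequence is a 90% half-width that stratification would shorten by 0 to 0.2 points from 3.54, and an analytic one-sided type I error of 0.041 to 0.050 against a nominal 0.05. There is no bias and no inflation, and simulated power is about 97% either way.

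These figures rest on 945 evaluable participants, 12.5% failure, and an assumed ICC of 0 to 0.10; the simulation also rests on assumed site sizes. The article gives neither the ICC nor the site sizes. The primary non-inferiority test is not undermined. The reason to act is consistency between design and analysis at almost no cost.

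**What to change.** 1. Make the primary estimate a risk difference stratified by site, for example Mantel-Haenszel: RD = Σ wₖ(x₁ₖ/n₁ₖ − x₀ₖ/n₀ₖ)/Σ wₖ with wₖ = n₁ₖn₀ₖ/nₖ. Treat the pilot cohort, which ran as a separate single-centre study, as its own stratum. Leave the 7.5-point margin and the 90% interval unchanged, and keep the unadjusted difference as a sensitivity analysis. If the team prefers not to alter the primary rule, the stratified estimate should at least be a pre-specified sensitivity analysis.
2. Separately, add site to the adjusted logistic model, and state that the result will be reported as a standardised (marginal) risk difference with its confidence interval.

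The cost is wording and minor extra analysis work, with no new data. The change must be fixed before the SAP is locked. Given the earlier amendment of the margin, the record should show that it was made without sight of results by arm.
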